### Randomization

The design involves three conditions (*n* = 30 per condition; *N* = 90) to which recruited children will be assigned randomly upon confirmation of all inclusion criteria. One of the principal investigators of this study who is only occasionally involved in training and testing participants executes the randomization. A block randomization procedure is applied, and balancing the conditions for age, gender, and ADHD medication stratifies the randomization.

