#### Primary outcome measures

Mean group scores of every condition will be calculated for all primary outcome measures. The C3-P and C3-T [42] assess ADHD symptoms as rated by parents and teachers at pre- (t_0_), midway (t_1_), post- (t_2_), and follow-up test (t_3_), hence allowing us to assess changes within and between conditions from pre- to midway, from pre- to post-, and from pre- to follow-up test. Furthermore, at pre- (t_0_), post- (t_2_), and follow-up test (t_3_), brain activity, i.e. the mean levels of oxy-Hb and deoxy-Hb at various channels across different cortical areas, is assessed using fNIRS data as well as EEG data from the *n*-back task assessing working memory, the Go/NoGo task assessing response inhibition, and the VFT assessing general brain activity. Consequently, changes within and between conditions in brain activity from pre- to post-, and from pre- to follow-up test can be assessed. In addition, behavioural data (i.e. mean reaction times, mean reaction time variability (*SD*), and the mean total number of commission and omission errors) are obtained from the *n*-back task and the Go/NoGo task at pre- (t_0_), post- (t_2_), and follow-up test (t_3_), hence allowing us to assess changes from pre- to post-, and from pre- to follow-up test within and between conditions.

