Children with ADHD experience poor school performance [6–8] as well as a core deficit in self-control [3], that is, “the deliberate, conscious, effortful subset of self-regulation” [82]. However, aspects often neglected in prior studies include the effects of NFT and BFT on self-control and school performance. Depicting NFT and BFT as interventions that train the exertion of self-regulation in two domains, namely self-regulating an endogenous parameter and self-regulation of behaviour, it seems plausible to expect effects on and to assess self-control while investigating effects on the self-regulation of brain activity and behaviour. Furthermore, as poor school performance is related to difficulties in behaviour, EF, and self-control [8], and both NFT and BFT have been shown to improve behaviour and EF (e.g. [83, 84]), we should expect all three interventions administered in this study to improve school performance. Hence, it is vital to assess the effects of a NIRS-based NFT and an EMG-based BFT on school performance.

The present study is limited in that participants, parents, and the trainers administering the intervention are not blinded — even though an official debriefing of parents and children as well as communication of individual results will only take place after finishing the study, hence, after the follow-up test is completed. First, participants, parents, and trainers are not blinded due to time constraints that make it impossible to use both the NIRS machine and the EMG equipment simultaneously. Second, participants either wear or do not wear the HMD, and hence they will know whether it is the 2D or VR condition they belong to. Third, as measurements during training sessions require constant observation of the data being recorded, it is impossible to blind trainers for the kind of intervention administered. However, participants, parents, and trainers are informed that every participant receives a potent intervention. Hence, we hope that bias is reduced to a minimum.

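### The principal investigator who executes the block randomisation also, occasionally, trains and tests children, an overlap that nothing in the article requires

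*Protocol article*

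**What the plan says.** The Randomization section of the protocol article describes three arms of 30 children each. On timing it says that "recruited children will be assigned randomly upon confirmation of all inclusion criteria". On the person it says: "One of the principal investigators of this study who is only occasionally involved in training and testing participants executes the randomization". On the method it says: "A block randomization procedure is applied, and balancing the conditions for age, gender, and ADHD medication stratifies the randomization". Block size is not given, and the article does not say who confirms eligibility.

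On blinding, the Discussion states that "participants, parents, and the trainers administering the intervention are not blinded". It gives three reasons: NIRS and EMG equipment cannot both be used within the available time, the head-mounted display is visible, and trainers must watch the recorded data, so that "it is impossible to blind trainers for the kind of intervention administered". The article describes no blinded testers.

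Under Primary outcome measures, the Conners 3 questionnaires "assess ADHD symptoms as rated by parents and teachers". The other primary outcomes are fNIRS and EEG recorded during the n-back, Go/NoGo and verbal fluency tasks, and reaction times and errors from the n-back and Go/NoGo tasks. Digit span, mathematics, reading and writing are listed under Secondary outcome measures.

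**The concern.** Two safeguards are weakened when one person both executes the randomisation and has contact with participants.

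The first is concealment of upcoming allocations. Anyone who has carried out the earlier assignments in a stratified block scheme knows how each block has filled and can sometimes deduce the next arm. If that person also had a say in when a child is confirmed as eligible, the order of entry could follow the allocation.

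The second is assessment. This person has assigned the child and so tests with the arm known. The arm may already be known at baseline: under Time points of assessments, eligibility is checked at t_−1_ and baseline follows at t_0_, so if assignment comes directly after confirmation, baseline testing also comes after assignment.

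The second and third hypotheses are comparisons between arms, in a single-centre trial with unblinded participants, parents and trainers. Separating the randomiser from contact with participants is one of the few inexpensive protections still available.

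**Working it through.** The plan states no figure on this point, so there is none to reproduce. The check has three parts.

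**1. Does a stated reason require the overlap?** The Discussion's three reasons (equipment time, visible display, monitoring of recordings) all concern blinding during training. None concerns who randomises. The stated mitigations are that debriefing waits until after follow-up and that everyone is told each child receives a potent intervention. Neither touches allocation, or a tester who knows the arm. The overlap is therefore stated outright and left unexplained.

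**2. How predictable is the next arm to someone who knows past allocations?** Inputs: three arms at 1:1:1 (Randomization section); block size assumed to be 3, 6 or 9 and known to the person; past allocations within the stratum known; blocks completed.

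*Share of assignments that are certain.* An assignment is certain once only one arm has places left, that is, during the run of identical arms that ends the block. With k places per arm and block size b = 3k, the expected share is (1/b) × Σ P(last j places are the same arm), for j = 1 to k.
- b = 3: 1/3 = 33.3%
- b = 6: (1 + 1/5)/6 = 1.2/6 = 20.0%
- b = 9: (1 + 2/8 + 2/8 × 1/7)/9 = 1.2857/9 = 14.3%

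*Share of correct best guesses*, always naming the arm with most places left:
- b = 3: (1/3 + 1/2 + 1)/3 = 61.1%
- b = 6: (0.333 + 0.400 + 0.500 + 0.533 + 0.600 + 1)/6 = 3.367/6 = 56.1%
- b = 9: 53.2%, by exact enumeration of the block's states

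Chance is 33.3%. These are averages over completed blocks. Certainty comes only at the end of a block, and a trial of 90 children stratified by three factors may leave blocks unfinished, which lowers the certain share. The figures describe how far allocation could be foreseen. They are not an estimate of bias in any outcome.

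**3. Which outcomes could a tester who knows the arm affect directly?**
- Conners 3: rated by parents and teachers. The tester does not score it; only an indirect route through delivery of training remains.
- n-back and Go/NoGo: key presses logged by computer. Scoring is not open to the tester; instruction and conduct of the session are.
- fNIRS and EEG: recorded by instrument. Again only the conduct of the session is exposed.
- Verbal fluency: someone must apply the rules on proper names and compound words. The task enters the primary outcomes only through the brain recording; its word scores are not listed there.
- Digit span, reading and writing: examiner-administered, all secondary. The article reports interrater reliability of .998 for the writing test, so scoring latitude there is small.

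**The case against.** The strongest reply is that the article says much less than a critic might build on it. A reader might infer that this investigator holds the allocation list, knows every upcoming arm and can steer who enters which arm. The documents do not support that. The article mentions no list, does not say who generated the sequence or whether it is concealed, and gives this person no role in recruitment or eligibility. Recruitment runs largely through outside practices, schools and media, and most criteria (grade, diagnosis, IQ limit, reported illnesses) leave limited room for discretion. A condensed article may leave block size and concealment to the full protocol, so silence on them is not a finding. All of this stands: influence on enrolment is a possibility only.

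A reader might also infer that the primary outcomes are compromised. That goes too far, since the Conners ratings and key-press data are not scored by the tester, and the involvement is described as only occasional.

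Finally, a tester can learn the arm through training contact whoever randomises. That is true, and separating the roles does not cure it.

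What remains is the stated overlap. Occasional involvement limits its extent but does not separate the roles, and nothing in the article explains why they need to be combined.

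**Conclusion.** The point holds as an inexpensive improvement to a stated design choice. The person executing a stratified block randomisation has occasional training and testing contact, knows past allocations, may foresee some upcoming ones, and tests with the arm known.

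The predictability figures (33%, 20% or 14% of assignments certain) rest on assumed block sizes, a block size known to the person and completed blocks. The effect on any outcome cannot be quantified, because the number of sessions this investigator covers is not reported. Direct exposure is mainly in examiner-administered tests, mostly secondary, and in how test sessions are run. The documents do not show that enrolment has been influenced or that the between-arm comparisons are invalid.

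**What to change.** For the remaining children (the article reports the trial as ongoing), replace the sentence naming the principal investigator with wording such as: *Randomisation is executed by a department member, or a web tool, with no part in recruitment, eligibility decisions, training or testing. Each assignment is released only after the child has been irrevocably entered.* State that the investigator who has randomised so far no longer trains or tests participants.

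For children already in the trial, report by arm and time point how many training and test sessions that investigator covered, and add a sensitivity analysis leaving out only those assessments. Say explicitly that the rule under Statistical evaluation of the results, which drops all later measurements after a missing (neuro-)psychological test, is not applied here. Its rationale is practice effects; these children did take the test, so their practice history is intact. Because a standard repeated measures ANOVA would drop a child with an omitted time point, name the method that keeps the remaining data, for example a mixed model.

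The cost is slightly less flexibility in the rota and one extra analysis. Sample size, outcomes and interventions stay as they are. The change does not blind the other testers; that would need a separate provision.

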### Interventions

Two conditions involve 15 sessions of a NIRS-based NFT, one in a VR classroom setting and one in a 2D classroom setting to control for specific effects of trainings in VR and 2D. The third condition involves an EMG-based BFT in VR and constitutes a control condition that allows the evaluation of effects that are uniquely attributable to the NFT itself.

Every training session lasts approximately 60–70 min including a preparation phase at the beginning (20 min), in which the NIRS cap and optodes are fitted to the head, or the EMG electrodes are placed on both musculi supraspinatus and both mastoids. For the participants in the VR classroom setting, the head-mounted display (HMD) is mounted. The training sessions also include the NFT or BFT (45 min) and a training phase with stimulus cards at the end of the training sessions 6–15 (5 min). The stimulus cards present a screenshot of the 2D screen. Within the laboratory setting, these cards are introduced as cue stimuli associated with brain activation or increased muscular activity of the musculi supraspinatus as learned during the NFT or BFT. When employed at home, they are thought to facilitate activation and to establish an association between, for instance, doing homework and brain or muscle activation [44].

Every training session with NIRS-based NFT or EMG-based BFT consists of three blocks, of which the first and the second are with continuous performance feedback (feedback condition). In the third block, no contingent performance feedback is provided (transfer condition), which is thought to foster generalization of acquired self-regulation skills to real-life situations [45]. For the NIRS-based NFT, the first and the second blocks consist of 12 trials, the third of 8. Each trial starts with an active phase of 30 s in which the respective endogenous parameter, that is oxy-Hb in the bilateral dlPFC for NIRS-based NFT, should be regulated and is followed by a resting phase of 20 s at the end. For the EMG-based BFT, the first and the second block consist of 24 trials; the third block consists of 16 trials. Each trial starts with an active phase of 15 s in which muscular activity of the musculi supraspinatus should be regulated and is followed by a resting phase of 10 s. Durations of active and resting phases in NIRS-based NFT and EMG-based BFT conditions vary due to different response times of the respective endogenous parameters towards the beginning of self-regulation processes employed by the participants [46, 47]. Among the conditions, the amounts of trials are varied in order to obtain an equal total training duration for all conditions.

Lighting in the VR and 2D classroom provides the feedback. For the NIRS-based NFT, lighting increases with increasing activity in the bilateral dlPFC, i.e. increasing oxy-Hb, and decreases with decreasing activity, i.e. decreasing oxy-Hb. Lighting for the EMG-based BFT increases with increasing muscular activity in the right musculus supraspinatus compared to the left and decreases with increasing activity in the left musculus supraspinatus compared to the right.

During the first eight training sessions, the training follows a protocol with 50% activation and 50% deactivation trials. For the second half of the training sessions, the protocol changes to 80% activation and 20% deactivation trials. At the beginning of each trial, an arrow appearing on the blackboard of the VR or 2D classroom pointing upwards indicates an activation trial, while an arrow pointing downwards indicates a deactivation trial.

After eight training sessions, participants have a break of 2 to 3 weeks that should further support transfer to real-life settings by using stimulus cards with screenshots of the training setting. The stimulus cards show the image of the classroom that participants see during the training with the arrow pointing upwards and will be introduced in the laboratory setting at the end of training session numbers 6, 7, and 8. Participants are instructed to look at the cards, employ activation strategies they learned during the training, and imagine increasing the lighting five to six times. After this activation task, they solve a riddle appropriate for their age and knowledge. For the break, participants are instructed to practice activation at home at least once per day prior to a situation that requires sustained attention, e.g. doing homework. For the rest of the training sessions, participants are asked to continue practicing activation at home. Furthermore, they still practice with the cards at the end of every training session. The 2D and VR classroom is shown in Fig. 1. An overview of the study course is presented in Fig. 2.

**Fig. 1 Fig1:**
[figure not shown]
2D and VR classroom

**Fig. 2 Fig2:**
[figure not shown]
Flow chart showing the course of the study

### Positive reinforcement

In both NFT and BFT, an animated teacher in the VR or 2D classroom provides reinforcement via positive auditory feedback if the participant performed successfully in the past trial. In addition, smileys appear on the blackboard of the classroom to provide positive reinforcement at the end of every successful trial. Success is calculated as follows. For the NIRS-based NFT, a baseline is calculated as the average oxy-Hb signal from the eight dlPFC channels (four on the left and four on the right hemisphere) in the last 5 s before the start of each trial. For the EMG-based BFT, the baseline is calculated as the average normalized EMG output (right musculus supraspinatus EMG output minus left musculus supraspinatus EMG output) in the last second before the start of each trial. Reinforcement is provided with one smiley when the participant has spent 60–69% of the time of the second half of the trial on the required side of the baseline. For the NIRS-based NFT, below the baseline is a decrease in the oxy-Hb signal from the eight dlPFC channels, and above is an increase in the oxy-Hb signal from the eight dlPFC channels. For the EMG-based BFT, below the baseline is an increase in the activity in the left musculus supraspinatus compared to the right, and above is an increase in the activity in the right musculus supraspinatus compared to the left. Analogously, the participant receives two smileys with 70–79% and three smileys with at least 80% of the second half of the trial spent in the required direction. Furthermore, reinforcement for the second block changes adaptively with the performance in the first block. If the participant scored between 40 and 60% success rate in the first block, the second block will remain exactly like the first. If the participant achieves lower than a 40% success rate, the threshold will decrease to .8 standard deviations (*SD*) in either direction relative to the baseline, so that fluctuations in the light are more sensitive to performance. In addition, the threshold for receiving smileys would decrease to 50%, 60%, and 70% of the time that must be spent on the required side of the baseline, for one, two, or three smileys, respectively. If the participant scores higher than a 60% success rate in the first block, the threshold increases to 1.2 *SD* above and below the baseline, hence making changes in the lighting, requiring more relative activation or deactivation. In addition, the baseline is artificially augmented to be .1 *SD* above or below the calculated baseline. Consequently, in order to receive smileys, the participant has to maintain a stronger activation or deactivation than before. The third block will be calculated in the same way as the second.

### The VR and 2D classroom

In the VR and 2D classroom, every participant is seated at a virtual table in the second row of a primary school classroom (see Fig. 1.). Other pupils surround him/her, and a teacher sits in the front of the classroom at a desk. Visual, auditory, and mixed distractors such as, for instance, paper planes flying through the room, fellow students whispering, or people knocking on the door will be randomized to occur in 50% of all trials. Their appearance is balanced between trials and sessions, and the distractors appear with a distance of at least 60 s between two distractors.

### Token system

Children are rewarded for their participation. At the beginning of the study, they receive a sticker album and one sticker per test or training session in the course of the study. If participants report to have trained regularly with the stimulus cards during the break, they can earn two more stickers.

### Adverse events

Reported adverse events and other unintended effects of the interventions employed in this study or the trial conduct are recorded and discussed with psychologists as well as child and youth psychiatrists.

### Assessments

#### Culture Fair Intelligence Test 1-R and 20-R

The Culture Fair Intelligence Test 1-R (CFT 1-R) [48] is a non-verbal intelligence test that can be used for children aged 5 years and 3 months to 9 years and 11 months. It consists of five subtests on substitutions, mazes, classifications, similarities, and matrices. The test can be applied in a short and a long form that differ in testing time only, but not in the amount of subtests applied. The short form will be used in this study. Reliability scores for the subtests vary between *r* = .75 and *r* = .90, and reliability for the short form is reported to be *r* = .94. Retest reliability with a second measurement after 2.5 months is *r* = .90 [48]. For children aged 8 years and 5 months and older, the Culture Fair Intelligence Test 20-R (CFT 20-R) [49] is used. The CFT 20-R is a non-verbal intelligence test consisting of two parts, each containing four identically constructed subtests on completing series, classifications, matrices, and topological reasoning. In this study, the test is applied in its short version, which consists of only the first of the two parts. The reliability of the CFT 20-R is *r* = .92 for the short version of the test. The retest reliability is adequate, with *r* = .85 after 2 months [49]. Hence, both tests show adequate psychometric properties to measure intelligence in the study sample.

#### Conners 3rd Edition (Conners 3) - German translation

The German long versions of the Conners 3 for parents (C3-P) and teachers (C3-T) consist of 108 items for parents and 112 items for teachers. The Conners 3 tools assess ADHD symptoms but also learning problems, EF, peer relationships, and aggression/defiance [42]. Furthermore, the questionnaires contain screener items for anxiety and depression. Both versions of the Conners 3 have adequate psychometric properties for teachers and parents with good internal consistency for most of the scales (Cronbach’s α > .85) and acceptable values for the remaining scales (Cronbach’s α > .70). Test-retest reliabilities are also good, with average values of about *r* = .85. Consequently, the Conners 3 in its German version seems to be appropriate to assess the effects of the intervention administered in this study.

#### Strengths and Difficulties Questionnaire

The Strengths and Difficulties Questionnaire (SDQ) consists of 25 items and assesses behavioural strengths and difficulties of children on five scales: prosocial behaviour, hyperactivity, emotional problems, peer relationships, and conduct problems [43]. Different versions for teachers and parents are available and are used in this study. The factorial structure of the original English questionnaires was also found for the German translations (SDQ-Deu) [50]. Psychometric properties for the German versions are good, with high internal consistency for the whole questionnaire (Cronbach’s α = .82) and at least acceptable scores for the subscales (Cronbach’s α between .58 and .76). The retest reliability is specified with *r* = .62 [51]. Consequently, the SDQ-Deu is an appropriate measure to assess effects of the therapeutic intervention of this study.

